**ABSTRACT**

The objective of this study will be to evaluate the efficacy of regular cleaning of the oropharynx on the incidence of symptoms associated with flu and colds. A total of 150 individuals will be randomized to one of the two experimental regimens and followed for a period of 90 days. The experimental regimes include: control, using toothpaste and a soft toothbrush; and test: using dentifrice, soft toothbrush, and mouthwash for gargling containing cetylpyridinium chloride (CPC) (0.075%) and zinc in an alcohol-free solution. All products are commercially available and will be provided by the research team. Participants will be instructed to brush their teeth twice a day for two minutes. Those allocated to the test regime will gargle with 20 ml of the mouthwash after each brushing. At the initial visit, participants will receive the products and instructions for use, as well as a daily log questionnaire. Participants will be asked to send their daily records once a week, using a messaging application. The proportion of days without any of the evaluated symptoms will be used as the main outcome. In addition, soft and hard tissue exams will be performed at the initial consultation, after 30 and 90 days of follow-up. Possible adverse events will be collected throughout the study. The groups will be compared using the chi-square test and the significance level will be set at 95%.

**Key-words:** Influenza, Oropharynx, Cetylpyridinium

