### Sample size

The sample size of 150 individuals (75 per group) was based on internal data from the sponsor of this study. It was determined that 60 individuals per group are needed for 80% power for the occurrence of flu-like symptoms. Considering the nature of the study and the demand for daily questionnaire responses, an attrition rate of 25% is assumed over the course of the study.

- - 1. Inclusion criteria

Individuals must meet all the following criteria:

1. Sign this informed consent form (ICF) (Appendix A);

2. Men or women, aged between 18 and 70;

3. Good systemic general health as determined by study investigators;

4. Availability of 90 days to participate in the study;

- - 1. Exclusion criteria

During the study, the following exclusion criteria will be considered:

1. Be participating in any other clinical study;

2. Being pregnant or breastfeeding;

3. Present a history of allergies to oral hygiene products, personal hygiene products, or their ingredients;

4. Have mouth irritation or use oral anesthetic sprays;

5. Have diabetes;

6. Be undergoing extensive dental treatment or oral surgery during the study;

7. Present immunocompromised (HIV, AIDS, immunosuppressive drug therapy);

8. Use complete dentures;

9. Have carpal tunnel syndrome or arthritis in the hands.

10. Participant who substantially fails to follow the required protocols;

11. Participant who fails to attend scheduled appointments;

12. Participant who is treated, during the study period, with medications that may interfere with the parameters being analyzed in the study;

13. Participant who is treated by a medical or dental service, and this may interfere with the parameters being analyzed in the study;

14. Participant who develops serious adverse reactions. The investigator will immediately record the information on the Adverse Reactions Form (Appendix B);

15. The participant who chooses to end their participation in the study;

16. Participant reports being pregnant during the study.

- 1. **Tests products**

Participants will be randomized into one of the following experimental regimens and will receive products as follows:

Group control:

● Colgate Maximum Cavity Protection® Toothpaste.

● Commercially available soft toothbrush.

Test Group:

● Mouthwash containing 0.075% CCP and 0.28% zinc lactate, in an alcohol-free base, commercially available in Brazil.

● Colgate Maximum Cavity Protection® Toothpaste.

● Commercially available soft toothbrush.

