### 4.4.5 Subsequent assessment

Subsequent evaluations will be performed after 30 and 90 days of use of the designated products. Participants will attend the research location to be evaluated and receive additional products, according to the group to which they were allocated. During these visits, an Oral Assessment of Soft and Hard Tissues will be carried out (Appendix D). A Visit Form (Appendix H) will be completed for all study participants.

After the 90 days of the experiment, all participants will be instructed to no longer use the products provided, returning to their normal oral hygiene habits. All unused products will be handed over to an assistant not involved in the clinical examination and will be discarded following Federal University of Pelotas waste disposal guidelines.

- 1. **Monitoring and discontinuity of participants**

All randomized research participants who receive the products will be monitored according to the following protocol:

Participants will be considered to have completed the study if they are re-evaluated at the end of 90 days. They will only be considered lost to follow-up if no contact was established during the completion of the study, and there is, therefore, insufficient information to determine the status of the research participant. Efforts will be made to determine the reasons why the participant did not return for the required visit(s) or the reasons for the participant's withdrawal from the study. Participants will exit the study if any of the following occur:

1. Participant who substantially fails to follow the required protocols;

2. Participant who fails to attend scheduled appointments;

3. Participant who is treated, during the study period, with medications that may interfere with the study parameters being analyzed;

4. Participant who is treated by a medical or dental service, and this may interfere with the parameters being analyzed in the study;

5. Participant who develops serious adverse reactions. The investigator will immediately record the information on the Adverse Reactions Form (Appendix B);

6. The participant who chooses to end their participation in the study;

7. Participant reports being pregnant during the study.

The researcher will be responsible for promptly notifying the Federal University of Pelotas Research Ethics Committee about all participants who leave the study prematurely and experience serious adverse effects.

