## **4.7. Statistical analysis**

Chi-square test will be performed for gender data, and an independent t-test for the age variable, to test the hypothesis that the groups present balanced distribution of variables. The proportion of symptom-free days (i.e., none of the 10 symptoms were present) will be used for the primary outcome variable. Chi-square test will be used to compare the proportion of symptom-free days for the experimental groups. Analysis of variance can be used to compare groups. Significance level will be set at 95%.

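### The primary proportion of symptom-free days has no stated denominator, analysis population or missing-day rule, although treatment for a respiratory illness can trigger exit or data exclusion

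*Combined protocol and SAP*

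**What the plan says.** Section 4.7 defines the primary outcome: "The proportion of symptom-free days (i.e., none of the 10 symptoms were present) will be used for the primary outcome variable". The abstract repeats it: "The proportion of days without any of the evaluated symptoms will be used as the main outcome". The comparison is given in one line: "Chi-square test will be used to compare the proportion of symptom-free days for the experimental groups". Neither place says whether the proportion is of days recorded, days in the study or all 90 days. Section 4.7 names no analysis population, no rule for unrecorded days or early leavers, and no sensitivity analysis.

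Other sections bear on which days will exist:

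- **Sample size:** "an attrition rate of 25% is assumed over the course of the study". The plan links this to the daily diary and uses it only to set the number randomised.
- **Section 4.5, completion:** "Participants will be considered to have completed the study if they are re-evaluated at the end of 90 days". No amount of diary data is required for that status.
- **Section 4.5, exit rules 3 and 4:** participants leave if they receive medication, or medical or dental treatment, that may interfere with the study parameters. The exclusion criteria repeat both rules as items 12 and 13.
- **Appendix H, question 6:** the visit form asks whether reactions, treatments, prescriptions or pregnancy justify leaving the participant's data out of the statistical analysis.
- **Appendix F:** every day has eleven items (one global, ten symptoms). A day with any symptom adds ten more (nine on interference, one comparison with the day before).
- **Sections 2 and 4.3:** the control group has no gargle and no placebo.

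**The concern.** The primary result cannot be computed uniquely from the plan, and the open choices are not neutral. A cold can lead to medication or a medical visit. Under section 4.5 that can end follow-up, and under Appendix H it can remove data already collected. The diary also asks most of participants on the days that count against the product: 21 items instead of 11. Each route could remove symptomatic days more often than symptom-free ones.

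Participants know whether they gargle, so diary-keeping, treatment-seeking and exit may differ by arm. The comparison itself could then be biased, in either direction. If the choice among denominators and populations is made after the data are seen, the result is also open to the charge that it was picked.

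**Working it through.** **1. The plan's own figures.** The sample-size section gives 60 per group, 25% attrition and 75 randomised per group. 60 × 1.25 = 75, so the 25% serves only to inflate the sample. (A 25% loss from 75 leaves 75 × 0.75 = 56.25 rather than 60; that is a separate matter.) Planned diary days: 150 × 90 = 13,500. If 25% leave evenly over time (assumption), the loss is 13,500 × 0.25 × 0.5 = 1,687.5 days, or 12.5%, before any skipped days.

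**2. One participant, several answers.** Take a 7-day cold starting on day 40, with exit that day (illustration).

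- Fully observed: 83/90 = 92.2%.
- Days recorded, including day 40: 39/40 = 97.5%.
- Days recorded, excluding day 40: 39/39 = 100%.
- All 90 days, missing counted as symptomatic: 39/90 = 43.3%.

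The plan does not choose among the last three.

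**3. Selective loss of single days.** Let S be the true symptom-free proportion, and q1 and q0 the chances that a symptomatic or symptom-free day is missing. On recorded days:

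observed = S(1 − q0) / [S(1 − q0) + (1 − S)(1 − q1)]

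The documents give none of these inputs. Assume S = 0.85 and q0 = 0.10, so S(1 − q0) = 0.765.

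| q1 | Calculation | Observed | Shift (points) |
|---|---|---|---|
| 0.10 | 0.765/(0.765 + 0.135) | 85.0% | 0 |
| 0.20 | 0.765/(0.765 + 0.120) | 86.4% | +1.4 |
| 0.30 | 0.765/(0.765 + 0.105) | 87.9% | +2.9 |
| 0.40 | 0.765/(0.765 + 0.090) | 89.5% | +4.5 |

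**4. Illness-triggered exit.** Simulation, all inputs assumed: 0.7 to 1.5 eight-day colds per person in 90 days, exit on the third day of a cold, about 24% leaving. Within-arm shift:

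- pooled days, the literal reading of a chi-square on days: about +1.3 to +1.4 points;
- leavers' data excluded, as Appendix H permits: about +2.2 points;
- mean of per-person proportions: about −0.7 to −0.8 points. It becomes about +0.2 (1 to 1.5 colds, about 25% leaving) if only two days of the cold are recorded before exit.

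The same kind of loss thus moves the result by −0.8 to +2.2 points, a spread of 3.0, depending on choices that the plan leaves open.

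**5. Between arms.** Same formula, assuming q0 = 0.20.

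- No true effect (0.80 in both arms), equal loss: difference 0.
- True 0.80 v 0.85, q1 = 0.50 in both: 0.901 − 0.865 = 3.6 points instead of 5.
- No true effect (0.80), q1 = 0.50 in one arm and 0.25 in the other: 0.865 − 0.810 = 5.5 points, in favour of the arm that loses more symptomatic days.

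**The case against.** **The plan never says that recorded days are the denominator.** Correct. A reader might infer that the proportion is taken over whatever diary days exist. That is the likely default, but the documents leave the denominator undefined.

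**The 25% is not a rate of days lost through illness.** Also correct. It is participant attrition, attributed to the burden of the diary. Only two of the seven exit rules concern treatment, both depend on possible interference with study parameters, and section 7 leaves continuation under necessary concomitant drug therapy to the investigator. A reader might conclude that missing days are bound to be tied to being ill. The documents show only that they can be.

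**Illness-triggered exit does little harm.** On the mean of per-person proportions the shift can be as small as +0.2 points. That is not the only reading: a chi-square on days points to pooled days, where the shift is about +1.4. The objection shows that the answer depends on the unit, which the plan does not fix.

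**There are safeguards.** Photographs are due weekly, the paper set is handed in at day 90, and substantial failure to follow the protocol leads to exit. These reduce casual loss. They do not say how a missing day is analysed, and that exit rule itself ends follow-up.

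**The bias has no benchmark.** A reader might want to say that it rivals the effect sought. The documents state no effect: the size rests on unreported internal data and concerns the occurrence of symptoms ("It was determined that 60 individuals per group are needed for 80% power for the occurrence of flu-like symptoms"), not the proportion of days. No such comparison can be made.

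**Conclusion.** The point holds as a conditional risk in an incompletely specified primary analysis. Sections 4.5 and 4.7 and Appendix H, followed together on recorded days, allow data to be lost in a way related to the outcome, so this is more than missing detail. Within an arm, the assumed scenarios inflate the proportion by 1.4 to 4.5 points (selective loss of days) or by about 1.4 to 2.2 points (illness-triggered exit on pooled days, or with leavers excluded). All of these rest on assumed symptom, loss and exit rates, because the documents give none.

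It does not follow that the treatment comparison will be biased, or biased towards the mouthwash. With equal loss and no true effect it is unbiased. With equal selective loss a real effect is attenuated. Unequal loss, possible because participants know whether they gargle, can favour either arm. The change should be made before anyone sees data by arm.

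**What to change.** Amend section 4.7 to state the following.

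1. **Population and outcome:** all randomised participants, in the arm assigned, over the 90-day period, analysed by each participant's proportion of symptom-free days.
2. **Data kept:** all recorded diary data. Nothing is excluded because of treatment or illness after randomisation. Appendix H question 6 and the exit rules in section 4.5 must be reconciled with this analysis set, and section 4.5 with section 7.
3. **Day status:** symptom-free only if all ten items are 0; symptomatic if any item is 1 or more; otherwise missing.
4. **Main handling:** multiple imputation of missing days within arm, using adjacent days, study day and baseline covariates. This is valid only if days are missing at random given those data.
5. **Sensitivity analyses:** because imputation does not cover symptom-dependent loss, pre-specify (a) missing counted as symptomatic and (b) a tipping-point analysis that shifts the imputed values. The first is a bound: with a true 80% and 25% of days missing at random, it gives 0.75 × 80% = 60%.
6. **Reporting:** missing days and exits by arm and reason.

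The cost is SAP wording, modest programming and slightly wider intervals, with no new visits or participants. This is a cheap improvement.

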## **4.4. Experimental procedure**

### 4.4.1. Selection of participants

Research participants who sign the informed consent form and answer to the health questionnaire (Appendices A and C) will receive an intraoral clinical examination to identify whether they meet the inclusion and exclusion criteria. All individuals will receive an assessment of their soft and hard oral tissues, findings will be recorded on the Hard and Soft Buccal Tissue Form (Appendix D). The initial questionnaire will be recorded on the Initial Examination Form (Appendix E). The first 150 individuals who meet the inclusion criteria, sign the consent form and the health questionnaire will be included in the study. After initial assessments, all individuals will receive a questionnaire to record daily symptoms associated with the flu and cold (Appendix F). This form will be delivered in physical format, with the questionnaire for the 90 days of the study, to facilitate completion by the participant. Once a week, participants must send photographs of their daily records. This will be sent via a messaging application. Participants will be reimbursed amounts compatible with internet packages. The research team undertakes to download the records and store them on devices on external physical drives, not connected to the internet. Messages will be deleted immediately after downloads. Furthermore, confidentiality of participants' data will be ensured throughout data storage and other procedures of this study.

The selection of participants will be of convenience based on a verbal invitation at the different clinics of the Dentistry Faculty of Federal University of Pelotas. In addition, recruitment may include posts on social media, which explain the main objectives of the present study. Those who express interest in participating in the study will receive the consent form in two copies and, after reading and signing it, will be evaluated based on the following exams:

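### The primary chi-square test names no unit of analysis; on its natural reading it treats up to 90 correlated days per person as independent, which inflates the false-positive rate

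*Combined protocol and SAP*

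**What the plan says.** Section 4.7 (Statistical analysis) defines the outcome: "The proportion of symptom-free days (i.e., none of the 10 symptoms were present) will be used for the primary outcome variable". The test follows: "Chi-square test will be used to compare the proportion of symptom-free days for the experimental groups". The next sentence adds: "Analysis of variance can be used to compare groups". It does not say on which variable, at which level, or when. The abstract names only one test: "The groups will be compared using the chi-square test".

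The daily data come from a diary given to each participant, "with the questionnaire for the 90 days of the study, to facilitate completion by the participant" (section 4.4.1). The sample size section counts people: "The sample size of 150 individuals (75 per group) was based on internal data from the sponsor of this study". It states 80% power with 60 per group for the occurrence of flu-like symptoms. Section 4.4.3 gives people who share a house the same regimen.

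The document mentions no per-participant summary, mixed model, generalised estimating equation (GEE) or robust variance.

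**The concern.** The person (or household) is randomised, but the outcome is recorded by day. A chi-square test on a table of symptom-free against symptomatic days by arm takes each day as an independent observation. The document itself gives reasons to expect otherwise:

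- The aim covers the duration of symptoms as well as their incidence, and duration means runs of consecutive days.
- The diary in Appendix F asks how the cold compares with the day before.
- Any non-zero score on one of ten items, tiredness and sneezing among them, makes a day symptomatic.
- The health questionnaire records smoking and asthma, and neither is a listed exclusion, so stable differences between people are likely.

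If within-person correlation is ignored, the standard error is too small and the test rejects too often when the mouthwash has no effect. This test decides the conclusion of a trial described as phase III.

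**Working it through.** **Inputs from the document.** 75 randomised and 60 evaluable per group (sample size section); up to 90 diary days per person (abstract, section 4.4.1); significance level written as 95%, read here as a two-sided alpha of 0.05 (section 4.7).

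**Input not in the document.** The within-person ICC of daily symptom status. A range is assumed.

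**The plan's own figures.** The 60 per group cannot be recomputed, because no effect size, event rate or standard deviation is given. The 75 equals 60 x 1.25. No false-positive rate is stated beyond the nominal level, which the formula below returns at ICC 0.

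**Number of observations if days are pooled.** 75 x 90 = 6,750 person-days per arm at most; 60 x 90 = 5,400 with 60 complete diaries per arm.

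**Formulas.** Design effect D = 1 + (m - 1) x ICC, with m diary days per person. Actual two-sided type I error of the unadjusted test = 2 x (1 - Φ(1.96/√D)).

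**Worked case, m = 90, ICC 0.05.** D = 1 + 89 x 0.05 = 5.45; √D = 2.33; 1.96/2.33 = 0.84; 2 x (1 - Φ(0.84)) = 40%.

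| Assumed ICC | D, 90 days | Type I error, 90 days | D, 60 days | Type I error, 60 days |
|---|---|---|---|---|
| 0 | 1.00 | 5% | 1.00 | 5% |
| 0.01 | 1.89 | 15% | 1.59 | 12% |
| 0.05 | 5.45 | 40% | 3.95 | 32% |
| 0.10 | 9.90 | 53% | 6.90 | 46% |
| 0.28 | 25.92 | 70% | 17.52 | 64% |

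At ICC 0.50 with 90 days the figure is 77%. The rejection rate passes 50% when 1.96/√D falls to 0.6745, that is D = 8.44 and ICC = 7.44/89 = 0.084.

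**Simulation with no treatment effect, 60 per arm, 90 days.**

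- Beta-binomial data (4,000 runs per setting, mean proportion symptom-free 0.7 to 0.9) agreed with the formula: 39-40% at ICC 0.05, 53-54% at 0.10, 70-72% at 0.30.
- Illness episodes alone, with no differences between people (3,000 runs per setting; assumed mean episode 3 to 10 days, one onset per 30 to 90 well days), gave 34-63%.
- A t-test on one proportion per participant, which for two groups is the same as analysis of variance, rejected in 4.1-5.8% across all these settings. Household clustering was not simulated.

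**What the analysis-of-variance sentence adds.** On participant proportions it would avoid the within-person problem. On the same pooled 0/1 days it would not: with 430 against 490 symptomatic days out of 5,400 per arm, analysis of variance and the uncorrected chi-square both give p = 0.0386.

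**The case against.** The best defence is that section 4.7 never says days are pooled. The sample size is stated in individuals and for the occurrence of symptoms, which fits a comparison of people with and without symptoms. A chi-square test on people would be valid apart from the shared-house allocation. This reading is not excluded, but it is the less natural one: it would need a cut-off to classify participants, none is given, and it would not compare proportions of days. What stands is that the unit is unstated, rather than explicitly wrong.

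Three stronger readings are tempting, and the document supports none of them:

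- A reader might infer that the plan has a false-positive rate of 40-70%. That range needs pooled days, 90 complete diary days and an ICC of about 0.05 to 0.28. The document gives no ICC, and smaller values or shorter diaries give lower rates.
- A reader might infer that an ineffective mouthwash would more often than not be declared effective. A rejection rate above 50% needs an ICC of about 0.084 or more, and about half of the rejections would favour control. Rejection rates of 40-70% mean false claims of benefit in about 20-35% of trials.
- A reader might infer that the two permitted tests must give very different p-values. That holds only if the analysis of variance uses participant-level values, which section 4.7 does not say.

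**Conclusion.** The concern holds in conditional form. The primary analysis does not name its unit. Its natural reading treats correlated days as independent, and nothing in the document adjusts for this or for shared-house allocation.

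The absence of any adjustment can be read directly from the text. The size of the inflation rests on the assumed ICC and the number of diary days, but even an ICC of 0.01 with 90 days triples the nominal error. The optional analysis of variance also leaves open which test decides the trial. For a primary analysis this needs correcting before the data are analysed.

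**What to change.** In section 4.7 and the abstract, replace the chi-square test and the optional analysis of variance for the primary outcome with one primary analysis:

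- For each participant, divide symptom-free days by diary days reported.
- Compare the arms with a linear model on this single value, using robust standard errors clustered on household.
- Report the difference in mean proportion with its 95% confidence interval.

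A GEE on daily status, clustered by household, could serve as a sensitivity analysis. It is not interchangeable with the primary analysis: with a logistic link it estimates an odds ratio, and with an independence working correlation it weights people by the days they reported. This matters when diaries are incomplete, and the plan assumes 25% attrition.

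The cost is wording and a little analysis work; no new data are needed. The standard error will be larger than the pooled test implies. The plan should also say that the 80% power in section 4.2.1 was stated for the occurrence of flu-like symptoms and has not been shown for this analysis. Power cannot be recomputed from the document, which gives neither an effect size nor a standard deviation.
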